### Randomization

Following inclusion, clients will be randomized using restricted randomization to obtain a balanced sample size between groups for each seminar. Therefore, we will use a randomization plan generator (www.randomization.com). The random allocation rule will be implemented according to the restricted shuffled approach, a kind of block randomization which we will perform in a 1:1 ratio [34]: every 2 people will be statistically paired and randomly assigned to either the IG (*n* = 64) or WLG (*n* = 64), after stratification by role, i.e., voluntary choice to participate either as an AC or OC prior to randomization. The randomization procedure will be performed by an independent researcher who is not involved in the study.

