### Study procedures

In the screening phase, interested persons will receive the study information and will be asked for the fulfillment of inclusion and exclusion criteria. The final decision whether the clients fulfil the inclusion criteria will be made in case conferences by the research team at the UW/H. After inclusion, clients will be randomly assigned either to the IG or WLG. Subsequently, they will be informed in which group they will attend the SC. About 1 week before the SC-VR seminar, the client will get their VR equipment via post. This includes an onboarding manual for setting up the VR headset and using the hand controller in an VR environment. About 2 days before the SC-VR seminar, there will be an individualized onboarding, partly via videoconference, in which the clients will get access and explore the VR seminar environment. We will assess study outcomes before the start (baseline) of the SC-VR seminar, at 2-week, 4-, 8- and 12-month follow-up. Baseline data will be scheduled no more than 5 days before the first SC-VR seminar (Fig. 1) and (Table 1).

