### Analysis

There will be no interim analyses. The only stopping guideline refers to the stop of recruitment 4 weeks before the start of the intervention due to organizational needs. Even if the number of participants is not reached at this time point, there will be no further recruitment at a later date. For *research methodology feasibility* measures, we will calculate screening, recruitment, randomization, and drop-out rates (RQ1.1, RQ1.2) as well as missing data in answering the outcome measures (RQ1.3) at baseline, 2-week, and 4-, 8-, and 12-month follow-up.

For *intervention feasibility* measures, we will use QCA and/or CQR to inform about the appropriateness of the VR environment to the needs of SCs and benefits as well as barriers of VR for the use of SCs (RQ2.1, RQ2.2, RQ2.6). The facilitator’s manual adherence will be calculated using *Cohen’s kappa* as a robust measure of interrater reliability, in addition to the percentage *(%)* of the agreement between the two raters. Overall treatment integrity for each SC-VR will be calculated as the percentage *(%)* of treatment components defined by the manual across sessions that will be implemented as planned [42] (RQ2.3). Clients’ compliance will be assessed by the percentage *(%)* of seminars attempted and completed (RQ2.4). The clients’ expectancy of the SC-VR seminar, as well as potential cybersickness and the level of immersion in the VR experience, will be assessed by mean scores (*M*), standard deviations (*SD*), and 95% *CI* of the data gathered (RQ2.5). Adverse events will be monitored and reported descriptively (RQ2.7).

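### Fixed pairs within role strata make up to half of the allocations predictable if assignment is rolling and visible to the team that decides eligibility

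*Protocol article*

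**What the plan says.** The Randomization section describes restricted randomisation, "a kind of block randomization which we will perform in a 1:1 ratio", in which "every 2 people will be statistically paired and randomly assigned to either the IG" (n = 64) or the wait-list group (n = 64). This is done "after stratification by role, i.e., voluntary choice to participate either as an AC or OC prior to randomization". The stated purpose is "to obtain a balanced sample size between groups for each seminar". On who does it: "The randomization procedure will be performed by an independent researcher who is not involved in the study".

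Study procedures gives the order of events. Eligibility comes first: "The final decision whether the clients fulfil the inclusion criteria will be made in case conferences by the research team at the UW/H". Random assignment follows, and clients are then told which group they will attend.

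The Blinding section says that clients are not told their arm. They learn only their seminar, and a cover story hides the fact that the earlier seminars form the intervention group and the later ones the wait-list group. Facilitators know the design. Blinding of the research team is not mentioned.

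The Analysis section sets one closing point for enrolment, the "stop of recruitment 4 weeks before the start of the intervention", with no recruitment afterwards.

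**The concern.** A block of 2 is the most predictable form of restricted randomisation. Once one member of a pair is assigned, the other is fixed. The block size is printed in the protocol, and role is known before randomisation, so stratifying by role does not hide the pattern. Anyone who knows the earlier assignments in a stratum can work out the next one whenever a pair is half filled.

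This matters if that person also takes part in the eligibility decision. Most criteria are factual (age, agreement to conditions, three acute exclusions). The central one, a psychosocial conflict that has stayed unresolved for some time, leaves room for judgement. Someone who knows the next arm could include, defer or decline a client accordingly, and the arms would then differ in ways that adjustment for baseline only partly removes. The between-group estimates are exploratory here, but the protocol intends to use the effects seen in this study to size a confirmatory trial, so a bias would be carried forward.

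The reason given for pairing is also hard to follow. Each seminar belongs to a single arm, so there are no two groups within a seminar to balance.

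**Working it through.** The article gives no figure for predictability, so there is none to reproduce.

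**Inputs**
- Block size 2, ratio 1:1, strata by role: Randomization section.
- 128 clients, 64 per arm, hence 128 / 2 = 64 pairs: Sample size calculation and Randomization sections. If both role strata have an odd number of clients, there are 63 complete pairs, so 64 is the upper figure.
- Not in the article, so treated as a range: whether assignment is one by one or in batches, and whether the eligibility team sees earlier assignments.

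**Case A: one by one, earlier assignments visible, block size known**

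The share of allocations that is certain in advance is the expected number of forced places at the end of a block, divided by the block size.

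- Block of 2: the orders are AB and BA, and the second place is always forced. 1/2 = 50%, so 128 × 1/2 = 64.
- Block of 4: of the 6 possible orders, AABB and BBAA force 2 places and the other 4 force 1. Expected forced places = (2 × 2 + 4 × 1) / 6 = 4/3. Share = (4/3) / 4 = 33.3%, so about 42.7 of 128.
- Block of 6: exact enumeration gives 25%, or 32 of 128.
- Blocks of 4 and 6 mixed in equal numbers: (4 × 1/3 + 6 × 1/4) / 10 = 28.3%, or about 36.3 of 128. This assumes the sizes are known. With undisclosed sizes it is an upper bound.

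The success rate of always guessing the arm with more places left is also informative:
- Block of 2: (0.5 + 1) / 2 = 75%, or 96 of 128.
- Block of 4: 70.8% by enumeration.
- Unpredictable assignment: 50%.

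**Case B: both members of a pair, or the whole cohort, are included before randomisation**

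Nothing is predictable when eligibility is decided: 0 of 128. The same holds if assignments stay hidden from the team until recruitment closes.

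**Range:** 0 to 64 of 128, that is 0% to 50%.

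**Does the independent randomiser change Case A?** No. The prediction needs only the previous assignment in the stratum and the published block size. Access to the list is not required.

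**Seminar rationale.** The Randomization section aims for balance between groups for each seminar. The Blinding section places earlier seminars in one arm and later seminars in the other. Read together, the aim can only mean equal filling of earlier and later seminars, in other words equal numbers per arm. A single 1:1 shuffle within each role stratum achieves that without pairs.

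**The case against.** The strongest objection is that the 50% depends on conditions the article never states. Pairing every two people can just as well mean that two clients already included are randomised together. Inclusion through case conferences and a single closing date for recruitment both fit batch randomisation. This stands, and it is why the result is a range.

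A reader might infer that unblinded staff decide eligibility and know every second allocation. The article does not support that. The Blinding section covers clients, assessors and facilitators only, and nothing says that the eligibility team sees earlier assignments. The inference is plausible, because whoever maintains the cover story knows that a seminar date reveals the arm and no concealment from the team is described, but it remains an inference. Nor are clients told their arm. The group they are told about can simply be the seminar group.

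A journal article may also leave the timing and concealment of allocation to the full protocol. That is fair, and their absence alone would be no finding. What remains is what the article does fix: a block of 2, printed, with a purpose that does not fit single-arm seminars.

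The consequences are limited as well. The proposed primary outcome is adherence, RQ3.2 and RQ3.3 ask for within-subjects effect sizes, and all analyses are declared descriptive and exploratory. Clients present themselves and the criteria are minimal, which leaves little room for steering. This lowers the stakes, but the between-group comparison in the mixed-design ANOVA would still be exposed.

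**Conclusion.** The point holds in conditional form. A fixed, published block of 2 within role strata makes up to 64 of 128 allocations (50%) certain in advance, provided that assignment is one by one and the research team deciding eligibility can see earlier seminar assignments. If pairs or the whole cohort are randomised together after inclusion, the number is zero. The article states no safeguard that rules out the first case, and the independent randomiser is not one.

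The balance rationale is unclear rather than impossible. It makes sense as equal numbers per arm within role strata and should say so.

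The change is worth making because the stated method is a weak choice, a better one is available at almost no cost, and the estimates are meant to inform a later trial. There is no evidence that allocation would be steered.

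**What to change.** 1. After recruitment closes, 4 weeks before the start, have the independent researcher randomise all included clients in one step, 1:1 within the active-client and observing-client strata. Nothing is then predictable when eligibility is decided.
2. Leave baseline where Study procedures puts it, no more than 5 days before the first seminar. Randomising only after baseline would not fit, because VR equipment is posted about 1 week before the seminar. Randomising at closure leaves about 28 − 7 = 21 days before posting for the first seminars.
3. If allocation has to be rolling, use randomly varied block sizes, for example 4 and 6, and do not disclose them.
4. Replace the wording about balance for each seminar with equal numbers per arm within role strata.

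**Cost:** a few sentences in the Randomization section. Under step 1, clients learn their seminar date later. Under step 3, an incomplete last block can leave an imbalance of at most 3 per stratum (half of a block of 6).

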### Blinding

#### Clients

They will not be informed about the design of this RCT, whether they will be assigned to the IG or WLG, and the specific study research questions. They will be informed about their randomized assignment to any of the SC-VR seminars. The cover story includes that the dates of the SC-VR seminars are as they were provided by the facilitators. It is not made public that the earlier group of SC-VR seminars refers to the IG and the later group of SC-VR seminars to the WLG. This procedure is closely related to the way in which participants come to SC seminars in natural settings. After study completion, all clients will be unblinded, and the design of the study will be published. All assessments at all points in time will be conducted online and pseudonymized, and no blinding of assessors will be needed.

#### Facilitators

The facilitators are informed about the study design as the original RCT [2–5] is well-known amongst them. Consequently, blinding was not possible without jeopardizing the facilitators’ trust in the study team.

### Facilitator’s training and supervision

All facilitators will participate in a 4- to 5-day training using VR technology and applying it to SC. The SC in VR technology trainings will take place in autum 2023 and will be conducted by a professional VR training institute: RAUM virtual collaboration and CONENT Conscious Entrepreneurship.

### Measures

As the purpose of this study is to explore the feasibility of a fully powered RCT, we will use different measures, including both qualitative information and quantitative data.

#### Feasibility and acceptability measures

##### Research methodology

RQ1.1 and RQ1.2: The feasibility of protocol implementation will include the ability to meet the total recruitment goal (*n* = 128), in the IG (*n* = 64) and WLG (*n* = 64) in particular. It takes the estimation of the total sample to be recruited into account, the total drop-out rate, and differential drop-out rate within the study arms at all measurement times. Data will be collected through the observation of the client flow: counting the number of interested persons who will (1) contact the recruiting office, (2) drop out by not giving consent, (3) drop out before the beginning of the SC-VR seminars, (4) start SC-VR seminar, (5) drop out during the SC-VR seminars, (6) end SC-VR seminar, (7) participate in the 2-week follow-up, (8) participate in the 4-month follow-up, (9) participate in the 8-month follow-up, and (10) participate in the 12-month follow-up. All clients must be abstained from taking part in any another SC until completion of the study. Success will be defined as the achievement of 100% of the planned sample and retaining 85% of the clients in the SC-VR intervention.RQ1.3: Outcome measure appropriateness will be assessed through the observation of missing data and the delay in answering the outcome measures. Success will be defined by missing data below 20% of the total data set and the answering of outcome measures within 3 days around the measurement date.

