**Design:**

We will perform a prospective, monocentric, parallel-group, feasibility RCT with subsequent intervention. A total of 128 clients of 3-day group-based SC-VR seminars will be randomized to either the intervention group (IG; *n* = 64) or wait-list group (WLG; *n* = 64), which receives SCs in VR after 4 months. *Feasibility and acceptability* of the (1) research methodology and (2) intervention as well as the (3) estimation of effect sizes will be assessed using qualitative and quantitative data. Based on the model of a general mental health, the *proposed primary outcome* includes the SC-VR adherence, and the *proposed secondary outcomes* refer to psychological functioning (OQ-45.2), social system functioning (EXIS), psychological distress (FEP-2), motivational incongruence (INK-SF), and goal attainment (GAS). We plan to investigate the short-term efficacy at 2-week and 4-month follow-up within the RCT design (*n* = 128), and mid-term efficacy at 8- and 12-month follow-up for the intervention group (*n* = 64).

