
## Methods

### Design

The study is designed as a prospective, monocentric, parallel-group, feasibility RCT with subsequent intervention. A total of 128 clients of group-based SCs in VR-seminars will be randomized to either the intervention group (IG, *n* = 64) or wait-list group (WLG, *n* = 64). Each study facilitator will conduct four SC-VR seminars in tandem-partnership. The short-term intervention outcome will be measured including three assessment points: baseline and 2-week and 4-month follow-up, with the latter representing the primary endpoint. In addition, we will assess mid-term effects at 8-month follow-up and long-term effects at 12-month follow-up.

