### Sample size calculation

Although feasibility studies, e.g., to develop an intervention, do not require a sample size calculation, it was important for us to ground the number of participants in our study on a statistical rationale that would allow a statement to be made about the sample size needed for a confirmatory trial. Cocks and Torgerson [31] used a confidence interval (CI) approach to calculate pilot sample sizes for continuous outcome measures. Supposed 0.3 of a standard deviation between two groups would be worthwhile, then such a study requires about 350 clients (assuming 80% power, two-sided alpha of 5%) in the final analysis of the fully powered RCT. Consequently, 32 clients (approximately 9% of the main sample size) would be required to produce a one-sided 80% confidence limit. A pilot trial with that sample size which finds an estimate larger than zero is supposed to demonstrate feasibility of a confirmatory RCT considering the recruitment and retainment of clients and so forth. According to this approach for two-arm feasibility RCTs, we will recruit a minimum of 32 clients. Since we are in the good position of sufficient personal and financial resources, we can include more clients in our study, and if possible, we will recruit 128 individuals, i.e., 64 clients in the IG and WLG, respectively (Fig. 1).

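### The retention and missing-data success rules are pooled over arms and measurement times, so neither directly tests completeness at the 4-month primary endpoint

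*Protocol article*

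**What the plan says.** The Design section of the Methods lists the assessments for the short-term outcome as "baseline and 2-week and 4-month follow-up, with the latter representing the primary endpoint". The planned sample is 128, with "64 clients in the IG and WLG, respectively".

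Under Feasibility and acceptability measures, Research methodology, success for RQ1.1 and RQ1.2 is full recruitment plus "retaining 85% of the clients in the SC-VR intervention". For RQ1.3 the article states: "Success will be defined by missing data below 20% of the total data set", together with "the answering of outcome measures within 3 days around the measurement date". The timing part has no percentage.

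The same section says that feasibility will take into account the "differential drop-out rate within the study arms at all measurement times". The Analysis section adds that the team will calculate "missing data in answering the outcome measures (RQ1.3) at baseline, 2-week, and 4-, 8-, and 12-month follow-up". Neither of these has a success threshold.

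On the schedule, the abstract speaks of "mid-term efficacy at 8- and 12-month follow-up for the intervention group". Table 1 lists the 8-month assessment without restricting it to an arm. Its footnotes limit only the 12-month assessment to the intervention group, and give the wait-list group a second 2-week assessment after its own seminar. According to the abstract, the wait-list group receives the seminar after 4 months.

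**The concern.** The study is meant to show whether a fully powered trial can be planned and run. The effect-size questions (RQ3.2, RQ3.3) concern change from baseline to 4 months, and the mixed-design ANOVA uses the 4-month wave in both arms. What a later trial most needs to know about the methodology is therefore whether 4-month data can be collected in the intervention arm and in the wait-list arm.

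The stated rules measure something else. Retention is defined on the seminar, which wait-list clients attend only after the 4-month point. It therefore bears on their 4-month completeness only indirectly: a client who attends was still in the study, but need not have answered the questionnaire. The missing-data percentage is taken over the whole data set, so nearly complete baseline and 2-week forms can offset losses at 4 months, and a complete intervention arm can offset losses in the wait-list arm. Both rules could be met while the 4-month comparison was seriously incomplete on one side.

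**Working it through.** The protocol states no figure for 4-month completeness, so there is none to reproduce. The check asks how much 4-month loss the stated thresholds let through.

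**Inputs.** 128 clients, 64 per arm (Sample size calculation); 85% retention and less than 20% missing (Research methodology); assessment waves from the abstract, Design and Table 1. Each client-assessment counts once, with equal weight.

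**Thresholds as counts.**
- Retention on all clients: 0.85 × 128 = 108.8, so at least 109 retained and at most 19 lost.
- Retention per arm, if it were applied that way: 0.85 × 64 = 54.4, so at least 55 retained and at most 9 lost.

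**Denominator of the missing-data rule.** Total = 64 × (assessments per intervention client + assessments per wait-list client).

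| Reading of the schedule | Per client, IG / WLG | Total | Most that may be missing below 20% |
|---|---|---|---|
| Three randomised waves only | 3 / 3 | 384 | 76 |
| 8 months in IG only, no second 2-week form | 5 / 3 | 512 | 102 |
| 8 months in IG only with the second WLG 2-week form (or 8 months in both arms without it) | 5 / 4 | 576 | 115 |
| Table 1 with its footnotes | 5 / 5 | 640 | 127 |

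**Case A: one-sided attrition.** Suppose 19 wait-list clients leave for good after baseline and no intervention client leaves.
- Pooled retention: 109/128 = 85.2%, pass.
- Loss at 4 months: 19/64 = 29.7% in the wait-list arm against 0% in the intervention arm.
- Missing data, three randomised waves: 19 × 2 = 38; 38/384 = 9.9%, pass.
- Missing data, Table 1 count: 19 × 4 = 76; 76/640 = 11.9%, pass.

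**Case B: the 4-month wave alone.** Suppose all 64 wait-list clients skip only the 4-month form and later attend their seminar.
- Missing data: 64/384 = 16.7%; 64/512 = 12.5%; 64/576 = 11.1%; 64/640 = 10.0%. All pass.
- Retention can be 100%, because seminar attendance does not depend on that form.

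**Case C: the whole wait-list arm leaves for good from 4 months.**
- Pooled retention: 64/128 = 50%, fail.
- Missing data: 192/640 = 30.0% and 128/576 = 22.2% fail; 64/512 = 12.5% and 64/384 = 16.7% pass.
- Both rules would pass only under the two narrower counts, and only if retention were judged in the intervention arm alone.

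**Effect of the proposed rule.** With at least 55 of 64 per arm required at 4 months, the wait-list arm has 64 − 19 = 45 in Case A and 0 in Cases B and C. All three fail.

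**The case against.** The strongest reply is that seminar retention does bear on the wait-list arm. Because that seminar follows the 4-month point, a retained wait-list client must still be in the study then. Judged on all 128, at least 45 of 64 wait-list clients (70%) would remain past 4 months. This stands, and it rules out the inference that the retention rule says nothing about the wait-list arm. It does not close the gap, because it still permits a loss of 29.7% on one side and does not require the 4-month form to be answered.

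A reader might also infer that the study could lose the entire wait-list arm at 4 months and still be called a success. The documents do not support that as a general statement. Permanent loss fails pooled retention at 50%, and Case B needs every wait-list client to skip one form and then attend, which is an extreme pattern. Case A needs neither assumption.

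The 3-day answering rule is a joint part of RQ1.3 success. Read strictly, it might catch Case B. With no percentage attached, however, that reading would let a single late form fail the study, so it cannot serve as a completeness threshold.

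Drop-out by arm and missing data by wave will be reported, so the loss would not be hidden. That also stands; what is lacking is a criterion attached to those figures. It is also fair that RQ1.3 asks how acceptable the questionnaires are, for which a pooled percentage is a reasonable gauge. But it is the only missing-data threshold that the article sets.

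The 8-month discrepancy may be no contradiction: data could be collected in both arms while mid-term efficacy is analysed in one. It matters here only because it leaves the denominator open.

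**Conclusion.** The point holds in a limited form. The two numeric rules are pooled over arms and measurement times, and no completeness threshold is tied to the 4-month follow-up or to either arm. Both rules can be met with 29.7% of the wait-list arm lost at 4 months and none of the intervention arm. In the extreme case where only the wait-list 4-month forms are missing, the missing-data rule is met under every reading of the schedule tried (10.0% to 16.7%).

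This rests on three assumptions: retention is judged on all 128 clients, each assessment carries equal weight, and the 3-day rule is not read as requiring every form on time. The 4-month primary endpoint here means the time point named in the Design section; the proposed primary outcome is SC-VR adherence, measured at the seminar. The weakness lies in the success criteria, not in data collection or reporting, and it should be corrected because the feasibility conclusion depends on those criteria.

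**What to change.** - Judge the rule of less than 20% missing separately by arm and by measurement time, at minimum for the OQ-45.2 at 4 months.
- Add a criterion for the share of randomised clients in each arm with a completed 4-month OQ-45.2. The existing 85% could be reused, which means at least 55 of 64 per arm.
- Keep retention in the seminar as a separate criterion for the intervention, and state whether it is judged on all clients or by arm.
- State which arms are assessed at 8 months, in the same way in the abstract and Table 1, so that the number of scheduled assessments is fixed.

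The cost is a change of wording. No new data are needed, since drop-out by arm and missing data by wave are already to be calculated. The downside is that success becomes harder to meet.
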